**Recording, Management, and Reporting of Adverse Events:**

1. **Recording:** All adverse events, regardless of severity or expectation, should be meticulously documented in the study records. The documentation should include a description of the event, its severity, start and end dates, management measures, outcomes, and an assessment of the association with the study treatment.
2. **Management:** For any serious or unexpected adverse events, appropriate therapeutic measures should be immediately taken. For instance, in the case of hypotension, measures such as reducing ultrafiltration and administering fluids to raise blood pressure should be implemented. In the event of an allergic reaction, timely administration of dexamethasone and antihistamines may be necessary, which could also include discontinuing the study intervention.
3. **Reporting:** All serious adverse events will be reported to the supervising physician regulatory authorities and the ethics committee within the stipulated timeframe. Additionally, in accordance with local regulations and protocol requirements, these events will be reported to the relevant regulatory bodies.

**Serious Adverse Events:**

1. **Reporting Method:** Researchers should utilize a pre-established reporting form to notify the study sponsor and the ethics review committee of serious adverse events. Concurrently, in compliance with local regulations and protocol mandates, these events should be reported to the relevant regulatory authorities.
2. **Management Measures:** Immediate and appropriate medical actions should be taken. If necessary, the patient's participation in the study should be halted, and a thorough diagnostic investigation should be conducted to determine the cause of the event.
3. **Follow-up Method:** Continuous monitoring and treatment should be provided until the event is resolved or stabilized. Follow-up information should encompass subsequent treatments, medical outcomes, and a final assessment.
4. **Timing:** A detailed timeline should be maintained, documenting the dates of event occurrence, identification, reporting, and resolution.

**IX. Quality Control and Assurance of the Study**

1. **Clinical Indicator Testing:** All clinical indicator tests will be conducted at West China Hospital to ensure consistency in operations and comparability of results. Participants will receive professional training and will follow standard operating procedures (SOP) during the testing process to minimize errors as much as possible.
2. **Implementation of SOPs:** To ensure consistency in the study, all study-related operations will be carried out in accordance with the pre-established SOPs. Researchers will receive training before the start of the study, including but not limited to technical operations, equipment use, and data collection standards, to ensure consistency and standardization of operations.
3. **Researcher Training:** All researchers will receive systematic training, including the study objectives, operational procedures, and ethical standards. Training will be regularly updated to ensure that researchers maintain a high level of understanding and execution of the study.
4. **Participant Compliance:** To ensure participant compliance, a regular communication and follow-up mechanism will be established. Researchers will establish good communication channels with participants, thoroughly explain the study process and its importance, and encourage and monitor participant compliance.
5. **Data Collection, Organization, and Analysis:** Data collection will use a unified data form to ensure the completeness and accuracy of the data. Data organization will be carried out by professional data administrators to check the completeness and logical consistency of the data. Data analysis will be completed by experienced statistical analysts using advanced analytical methods to ensure the credibility of the results.
6. **Study Monitoring:** The study will be subject to an independent monitoring mechanism, with professional monitors regularly checking the execution of the study, the authenticity of the data, and compliance. Monitoring reports will be promptly fed back to the research team to ensure that any potential issues are corrected in a timely manner.

The implementation of these quality control and supervision measures will help enhance the reliability of the study and the scientific nature of the results, ensuring the smooth progress of the study.

**X. Data Safety Monitoring**

Clinical studies will develop a corresponding data safety monitoring plan based on the level of risk. All adverse events will be meticulously documented, appropriately managed, and followed up until they are satisfactorily resolved or stabilized. Serious adverse events and unexpected events will be reported in a timely manner to the ethics review committee, competent authorities, sponsors, and drug regulatory departments in accordance with regulations. The principal investigator will conduct periodic cumulative reviews of all adverse events and convene investigator meetings as necessary to assess the risks and benefits of the study. In the case of a double-blind trial, emergency unblinding may be necessary to ensure the safety and rights of the participants.

**XI. Statistical Analysis**

SPSS software (version 27.0, SPSS Inc., USA) and R version 4.2 (R Foundation for Statistical Computing, Vienna, Austria) will be used for data analysis.

1. **Descriptive Statistical Analysis:** Basic characteristics of the study sample will be described, including demographic features, laboratory indicators, underlying diseases, etc. Descriptive statistical analysis will also be conducted on filter lifespan, filter performance indicators, and changes in patient physiological parameters across different blood flow rate groups, including mean values, standard deviations, medians, etc.
2. **Survival Analysis:** Survival analysis methods (e.g., Kaplan-Meier curves) will be used to compare differences in filter lifespan among different blood flow rate groups. Cox proportional hazards models will be employed to analyze factors that may affect filter lifespan, such as blood flow rate, patient age, underlying diseases, etc.
3. **Analysis of Variance (ANOVA):** Differences in filter performance indicators among different blood flow rate groups will be analyzed using ANOVA.
4. **Safety and Adverse Event Analysis:** The incidence of adverse events (e.g., thrombus formation, bleeding complications) among different blood flow rate groups will be compared using chi-square tests or Fisher's exact tests to assess the safety of CRRT treatment at different blood flow rates.
5. **Clinical Outcome Analysis:** Appropriate statistical methods will be used to compare clinical outcomes, such as renal function recovery, survival rate, and hospital stay duration, among different blood flow rate groups.

A P-value of less than 0.05 will be considered statistically significant.

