**II. Research Objectives**

1. **Primary Objective:** To evaluate the impact of different extracorporeal blood flow rates on filter lifespan in CRRT without anticoagulation. By comparing filter lifespans under different blood flow rates, the optimal extracorporeal blood flow rate will be determined to maximize filter lifespan, reduce the number of filter replacements during CRRT, lower treatment costs, and improve patient outcomes.
2. **Secondary Objectives:**
   1. To explore the performance and efficacy of CRRT filters under different blood flow rates, including creatinine clearance, urea nitrogen clearance, and ultrafiltration rate.
   2. To analyze changes in hemodynamic parameters and physiological indices of patients under different blood flow rates, including arterial blood pressure, to assess the impact on patient physiological status.
   3. To study the impact of different blood flow rates on adverse events during CRRT, such as thrombus formation and bleeding complications, to evaluate safety and feasibility.
   4. To assess the clinical outcomes of CRRT treatment under different blood flow rates, including renal function recovery, survival rate, and hospital stay duration, to determine the optimal treatment strategy.

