**VI. Detection Items and Time Points**

1. **Baseline Data:** At the time of patient admission, detailed records will be kept of demographic characteristics, laboratory indicators, examination results, primary disease, comorbidities, concomitant medications, blood pressure, etc.
2. **Filter Lifespan:** Each time a filter is replaced, the usage time of each filter will be recorded. Filters will be replaced based on the following criteria: obvious clotting in the filter, catheter, or venous chamber; filter usage time exceeding 72 hours (even if there are no other issues); patient needs to stop the machine for an outside examination or other treatments; treatment goals are achieved or CRRT is terminated.
3. **CRRT-Related Parameters:** After the CRRT prescription is established, detailed records will be kept of the CRRT prescription, including ultrafiltration rate, access, mode, etc. If the blood flow rate is reduced due to poor circuit performance or the anticoagulation method is adjusted due to coagulation function, the time, adjustment amount, and changes before and after adjustment will be recorded in detail.
4. **Filter Performance and Efficacy:** After CRRT is completed, the filter clearance performance will be recorded, including creatinine clearance, urea nitrogen clearance, cystatin C, and ultrafiltration rate.
5. **Patient Physiological Parameter Changes:** During CRRT, arterial blood pressure will be monitored every 2 hours, and the occurrence of hypotension and other hemodynamic instability events will be recorded.
6. **Adverse Events:** During CRRT, any adverse events that occur will be observed and recorded, including thrombus formation, bleeding complications, etc.
7. **Clinical Outcomes:** After CRRT is stopped, the patient's renal function recovery will be monitored, such as changes in creatinine and glomerular filtration rate. After discharge, the patient's survival status and hospital stay duration will be recorded.

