**VIII. Observation, Recording, and Management of Adverse Events**

In this study, adverse events refer to events during CRRT that cause CRRT to be urgently stopped or pose a life-threatening risk to the patient, with significant improvement after CRRT is stopped. Therefore, the observation of CRRT adverse events ends when the patient completely finishes multiple courses of CRRT.

Anticipated adverse events include hypotension, electrolyte imbalance, bleeding, or infection. The relationship between adverse events and study interventions is typically judged based on: 1) Temporal association: The event occurs within a specific time after CRRT initiation, or other causes of adverse events are excluded; 2) Known side effects of drugs or devices; 3) Whether the event disappears or alleviates after CRRT is stopped.

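### Secondary objective 2 asks how flow rate affects arterial pressure, but section XI only describes pressure changes and plans no between-arm comparison of them

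*Protocol*

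**What the plan says.** Section II, secondary objective 2, reads in part: "To analyze changes in hemodynamic parameters and physiological indices of patients under different blood flow rates, including arterial blood pressure". Its stated aim is to judge the effect on the patient's physiological state.

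Section VI item 5 collects the data: "During CRRT, arterial blood pressure will be monitored every 2 hours, and the occurrence of hypotension and other hemodynamic instability events will be recorded".

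Section XI item 1 names three things to be described by group: "Descriptive statistical analysis will also be conducted on filter lifespan, filter performance indicators, and changes in patient physiological parameters across different blood flow rate groups". The summaries it lists are means, SDs, medians and the like. Two of the three reappear with a comparison between groups:

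- Lifespan gets Kaplan-Meier curves and Cox models in item 2.
- For filter performance, item 3 says "Differences in filter performance indicators among different blood flow rate groups will be analyzed using ANOVA".

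Physiological change does not reappear. The open-ended wording of item 5 covers clinical outcomes, with renal recovery, survival and hospital stay as its examples.

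Item 4 says that adverse event incidence "will be compared using chi-square tests or Fisher's exact tests to assess the safety of CRRT treatment at different blood flow rates". Its examples are thrombus formation and bleeding; hypotension is not named there. Section VIII supplies the link: "Anticipated adverse events include hypotension, electrolyte imbalance, bleeding, or infection". The same section defines an adverse event as one that forces an urgent stop of CRRT or threatens the patient's life, with improvement once CRRT is stopped.

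**The concern.** The objective asks about the effect of a randomised factor, and the analysis assigned to it is a table of means, SDs and medians. Followed as written, section XI produces no planned estimate or interval for the pressure difference between arms.

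This matters because section I says higher flow may lower blood pressure and cardiac output in haemodynamically unstable patients, while the abstract states that adjusting flow poses no risk to patients. The primary objective is to identify an optimal flow rate. If 250 mL/min gave the longest filter life, readers would want to know what it did to pressure, with a measure of uncertainty. If the only formal comparison is a count of severe events, a moderate fall in pressure could go untested.

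**Working it through.** **Where each outcome named in section XI item 1 is analysed**

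| Outcome | Between-arm analysis in section XI |
|---|---|
| Filter lifespan | Item 2: Kaplan-Meier, Cox |
| Filter performance | Item 3: ANOVA |
| Changes in physiological parameters | None named |

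The remaining route for haemodynamics is item 4 read together with section VIII. It reaches hypotension only as an adverse event, and so only events within the narrow definition there.

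**Size of the loss.** The plan states no figure for this outcome that could be reproduced. It gives no pressure SD, expected shift, hypotension cut-off or hypotension rate. The following inputs are therefore assumptions, apart from the first number:

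- n = 162 per arm. Section III derives it for lifespan (153/0.95 = 161.05, rounded up) and counts it in filters. The abstract gives 486 cases, and 3 × 162 = 486. I take 162 as patients.
- Normal pressure, one value per patient, and a shift δ of 0.2 to 0.4 SD.
- Hypotension is a fixed cut on that value, with rate p0 of 10 to 40% in the comparison arm.
- Pairwise comparison, two-sided 0.05.

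Formulas:

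- Continuous power = Φ(δ/√(2/n) − 1.96)
- p1 = Φ(Φ⁻¹(p0) + δ) and p̄ = (p0 + p1)/2
- Binary power = Φ((p1 − p0)/√(2p̄(1 − p̄)/n) − 1.96)

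Example with δ = 0.3 and p0 = 20%:

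- Continuous: √(2/162) = 0.1111 and 0.3/0.1111 = 2.70. Φ(0.74) = 77.0%.
- Binary: p1 = Φ(−0.842 + 0.3) = 0.294 and p̄ = 0.247. The standard error is 0.0479 and 0.094/0.0479 = 1.962. Φ(0.002) = 50.1%.
- Loss: 26.9 points.

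Full grid, power in %:

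| δ (SD) | Continuous | p0 10% | p0 20% | p0 30% | p0 40% |
|---|---|---|---|---|---|
| 0.2 | 43.6 | 19.5 | 25.3 | 28.3 | 29.7 |
| 0.3 | 77.0 | 39.0 | 50.1 | 55.2 | 57.2 |
| 0.4 | 94.9 | 62.5 | 75.2 | 79.9 | 81.4 |

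The smallest loss is 94.9 − 81.4, about 14 points. The largest is 77.0 − 39.0 = 38 points. If 162 filters came from 81 patients per arm (two filters each, assumed), a 0.3 SD shift gives 48.0% continuous against 22.0 to 32.8% binary.

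The narrow event definition points to lower rates. At 162 per arm and 0.3 SD, binary power is 28.5% at a 5% rate and 18.0% at 2%.

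**Information retained.** For a normal variable, a yes/no cut keeps φ(z)²/[p(1 − p)] of the information in one continuous reading, where z is the cut point for event rate p:

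| Event rate | 5% | 10% | 20% | 30% | 50% |
|---|---|---|---|---|---|
| Retained | 22% | 34% | 49% | 58% | 64% |

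The figure falls below one half only for event rates under about 21%.

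A simulation used 14 readings per patient (28 h at 2-hourly intervals) and within-patient correlation of 0.3 to 0.7. It compared any hypotension with the patient mean. Relative efficiency was 0.26 to 0.34 at a 10% rate, 0.35 to 0.49 at 20%, and 0.41 to 0.56 at 30%.

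**The case against.** The best defence is that the model for a repeated secondary measure belongs in the SAP, which is not at hand, and that describing pressure by arm does not rule out testing it. This holds for model detail: no fault lies in the protocol's failure to name random effects or covariates. It does not fully answer the point, because section XI is not silent. It assigns pressure an analysis, and that analysis is description, in the same sentence as two outcomes that are then compared. A SAP that simply followed it would stop at description.

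A reader might go further and infer that the plan chose a yes/no count of hypotension to answer objective 2. The documents do not say so. Section XI names no test of hypotension. The stopping criteria in section IV mention it as a serious adverse event to be compared between groups, and section VI records it separately, but neither makes it the analysis for objective 2. Item 4 also does not fix the unit of incidence.

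A reader might likewise infer that most of the information is discarded, or that the test is known to be underpowered. Neither is established. For a single reading, more than half is lost only at event rates below about 21%, and the power grid itself reaches 81%. The grid also models hypotension as a cut on a normal value, whereas section VIII describes a clinical event.

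Two further objections stand. First, group means and SDs would show a fall in pressure, and a crude interval could be calculated from them, though not as a planned, baseline-adjusted analysis. Second, section VIII provides for treating hypotension by reducing ultrafiltration and giving fluids, so mean pressures may look alike while events differ. The event comparison should therefore not be demoted.

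**Conclusion.** The point holds in a limited form. A stated secondary objective about the effect of flow on arterial pressure, supported by 2-hourly data, is matched in section XI only by descriptive summaries. The one inferential route is adverse event incidence, reached by inference and confined to severe events.

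The cost in power cannot be calculated from the protocol. The loss of 14 to 38 points is illustrative. It rests on assumed normal shifts of 0.2 to 0.4 SD, hypotension rates of 10 to 40%, 162 patients per arm and a threshold model of hypotension. It should not be quoted as the power of item 4.

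This is a secondary-objective matter that should be corrected. It does not touch the primary outcome, the sample size or the conclusions about filter life.

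**What to change.** In section XI, add a between-arm comparison of the 2-hourly arterial pressures during CRRT, by assigned arm, as a secondary analysis for objective 2. A linear mixed model with patient as random effect, adjusted for pre-CRRT pressure and time, would serve. Report the arm differences (for example 250 v 200 and 150 v 200 mL/min) with 95% CIs.

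Report the between-arm comparison of hypotension events beside it, at equal rank, and state in item 4 that hypotension is included. The descriptive summaries can stay.

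The cost is one additional secondary model on data already being collected. The drawback is that pressure during CRRT is partly maintained by treatment, so mean pressure has to be read together with the event comparison.

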   - **Sample Size Calculation:** The primary outcome measure of this study is filter lifespan. Therefore, filter consumption quantity is selected for sample size calculation. Based on retrospective and prospective cohort study data from our center, the smallest difference in filter lifespan was observed between the 200 mL/min and 250 mL/min blood flow rate groups. Thus, the maximum possible sample size can be calculated based on the lifespan difference between these two groups. Previous study results showed that the average filter lifespan was 28.09 ± 21.15 hours in the 200 mL/min blood flow rate group and 35.51 ± 17.97 hours in the 250 mL/min blood flow rate group. With a significance level (α) set at 0.05 and power at 0.90, the software PASS (Power Analysis and Sample Size Software) version 15 was used to calculate a sample size of N = 153 per group. Considering a dropout and refusal rate of 5%, the final number of filters required per group is at least 162, totaling at least 486 filters.
2. **Research Methods**

Patients undergoing CRRT at West China Hospital who meet the inclusion and exclusion criteria will be randomly divided into three groups: low blood flow rate group, medium blood flow rate group, and high blood flow rate group. The international standard blood flow rate for anticoagulant-free CRRT is 250 mL/min, while the standard blood flow rate for anticoagulant-free CRRT at our center is 200 mL/min. For hemodynamically unstable patients or those with high circuit pressure, our center reduces the blood flow rate to 150 mL/min based on experience, which is consistent with previous studies defining 150 mL/min as the low blood flow rate group [1]. Therefore, we define 150 mL/min, 200 mL/min, and 250 mL/min as the low, medium, and high blood flow rate groups, respectively.

- **Low Blood Flow Rate Group:** Adjust the CRRT blood flow rate to 150 mL/min.
- **Medium Blood Flow Rate Group:** Adjust the CRRT blood flow rate to 200 mL/min.
- **High Blood Flow Rate Group:** Adjust the CRRT blood flow rate to 250 mL/min.

The remaining CRRT prescription and parameter adjustments will be determined based on the patient's actual condition, experienced clinical physicians, and CRRT specialists. If during CRRT, high blood flow rate causes high vascular access pressure and requires a reduction in blood flow rate, the following principles will be followed:

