**IV. Case Selection**

1. **Inclusion Criteria**
   1. Patients undergoing CRRT;
   2. Age 18 years or older;
   3. No anticoagulant used during CRRT;
   4. Informed consent provided by the patient or their legal guardian/agent.
2. **Exclusion Criteria**
   1. Patients with severe coagulation disorders or undergoing anticoagulant therapy;
   2. Patients receiving intermittent renal replacement therapy (IRRT) or other non-CRRT treatments;
   3. Pregnant women.
3. **Criteria for Study Termination**
   1. **Safety Issues:** Serious adverse events: If during the study, the incidence of serious adverse events related to treatment such as hypotension, malignant arrhythmias, or death is significantly higher in one group compared to the other two groups, or exceeds the predefined safety threshold, consideration should be given to terminating that group's study. The safety threshold is set based on data from similar previous studies and the opinions of clinical experts to ensure patient safety. For example, if the incidence of bleeding events exceeds 10% and is 5% or more higher than the other groups; the incidence of thrombotic events exceeds 5% and is 3% or more higher than the other two groups; the incidence of infectious events exceeds 15% and is 5% or more higher than the other groups; the incidence of cardiovascular events exceeds 8% and is 4% or more higher than the other two groups [2,3].
   2. **Inadequate Effectiveness:** Interim analysis: Interim analysis will be conducted after 50% of the patients have been enrolled, performed by an independent statistician who is blinded to treatment allocation.
   3. **Interim Analysis Objectives:** To assess filter lifespan in different blood flow rate groups, compare filter blockage rates among groups, and evaluate the incidence of adverse events.
   4. **Interim Analysis Indicators:** Primary outcome measure: Filter lifespan (hours); Secondary outcome measures: Filter clotting rate, incidence of adverse events (bleeding, thrombus formation, etc.).
   5. **Interim Analysis Method:** Kaplan-Meier survival analysis will be used to assess filter lifespan, and the Log-rank test will be used to compare differences in filter lifespan among different groups. The chi-square test will be used to compare differences in filter blockage rates and adverse event incidence among groups.

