   6. If the interim analysis results show that the filter lifespan in any group is significantly lower than the other groups (P < 0.05), and the incidence of adverse events is significantly increased, enrollment of patients in that group will be terminated. If there is no significant difference in filter lifespan among all groups (P > 0.05), and no significant difference in adverse event incidence, the study will continue until all patients have been enrolled.
   7. The statistician will report to the independent Data and Safety Monitoring Board (DSMB), which will review and assess the interim analysis data and provide recommendations to the researchers on whether to continue, modify, or terminate the study [4][5].
   8. **Achievement of Statistical Significance:** If the interim analysis shows a significant difference in filter lifespan among different blood flow rate groups (P < 0.05), and this difference is sufficient to prove the primary research hypothesis, the study may be terminated early.
   9. **Participant Request to Withdraw:** If a participant requests to withdraw from the study.

**Termination Procedure:** Upon receiving the DSMB's recommendation, the study leader should immediately suspend enrollment of new patients and notify all research centers; inform the Institutional Review Board (IRB) and relevant regulatory authorities, providing the reasons for termination and the interim analysis results; provide appropriate follow-up treatment and follow-up for patients already enrolled.

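### The final safety comparison rests on chi-square/Fisher tests that would miss excesses at the protocol's own example thresholds 57–72% of the time, and the interim rule built on the same test can contradict the safety-threshold rule

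*Protocol*

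**What the plan says.** Secondary objective 3 (section II) is to evaluate safety and feasibility through adverse events such as thrombus formation and bleeding. Section XI item 4 gives the method: incidence in the flow groups "will be compared using chi-square tests or Fisher's exact tests to assess the safety of CRRT treatment at different blood flow rates". The section closes with the general rule that "A P-value of less than 0.05 will be considered statistically significant". The section names no effect estimate, interval or reference difference for adverse events.

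Section IV.3 (Criteria for Study Termination) deals with safety twice.

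- **Item 1** says that terminating a group should be considered if serious events are significantly more frequent there, or if a safety threshold is exceeded. The first example is "if the incidence of bleeding events exceeds 10% and is 5% or more higher than the other groups". The others are thrombotic events above 5% with a gap of at least 3 points, infection above 15% with 5 points, and cardiovascular events above 8% with 4 points. The threshold limb needs no P-value.
- **Item 6** concerns the interim at 50% enrolment. If lifespan does not differ significantly "and no significant difference in adverse event incidence, the study will continue until all patients have been enrolled".

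The sample size (section III) uses filter lifespan alone: "28.09 ± 21.15 hours in the 200 mL/min blood flow rate group" against "35.51 ± 17.97 hours in the 250 mL/min blood flow rate group". "With a significance level (α) set at 0.05 and power at 0.90", PASS "was used to calculate a sample size of N = 153 per group", raised to 162 per group and 486 in total.

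**The concern.** A significance test supports a safety statement only if it would probably detect the harm that matters. The protocol gives examples of excesses serious enough to consider stopping a group, but the final safety analysis does not refer to them, and the sample size was not chosen to detect them. If the test usually misses differences of that size, P > 0.05 says little about whether a flow rate is safe.

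This matters because the primary objective is to identify an optimal flow rate, and the background section warns that higher flow may lower blood pressure and cardiac output in unstable patients. The rate with the longest filter life could be recommended alongside a null adverse-event test that carries little information.

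The interim raises a more direct problem. Non-significance for adverse events is part of a rule that the study continues, so the same data can point one way under item 6 and the other way under item 1.

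**Working it through.** **1. The protocol's sample size.** Difference 35.51 − 28.09 = 7.42 h; pooled SD √[(21.15² + 17.97²)/2] = 19.62 h. At two-sided α 0.05 and power 0.90, the normal formula gives 147 per group and the t-test 148. Dividing by the Wilcoxon efficiency of 0.955 gives 154–155, close to the stated 153. The protocol does not name the PASS test, so Wilcoxon is an assumption. Dropout: 153/0.95 = 161.05, rounded up to 162; 3 × 162 = 486. Adverse events play no part in this calculation.

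**2. Power of the safety test.** Inputs: 162 per arm (section III), α 0.05 (section XI), thresholds and gaps (section IV.3 item 1). Assumptions: 162 independent patients per arm, one arm at the threshold, and the other two lower by exactly the gap. The lower rates come from this subtraction; the protocol states no expected rates.

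The test statistic is X² = n Σ(pᵢ − p̄)² / [p̄(1 − p̄)] on 2 df, with critical value 5.99. Simulation (200,000 runs per row at each sample size) gives:

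| Event | Rates | Power, 162/arm | Missed | Power, 81/arm | Missed |
|---|---|---|---|---|---|
| Bleeding | 10/5/5% | 43.1% | 57% | 22.9% | 77% |
| Cardiovascular | 8/4/4% | 34.6% | 65% | 19.0% | 81% |
| Thrombotic | 5/2/2% | 33.9% | 66% | 17.2% | 83% |
| Infection | 15/10/10% | 28.0% | 72% | 15.4–15.6% (two runs) | 84–85% |

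The interim size is 486/2/3 = 81 per arm.

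Analytic check for bleeding: p̄ = 0.0667, and the noncentrality is 162 × [0.0333² + 2 × 0.0167²] / (0.0667 × 0.9333) = 4.34. This gives power of about 0.45, in line with the simulation.

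Variants at 162 per arm: pairwise chi-square misses 60–72% and pairwise Fisher 68–80%. With 153 per arm, the three-group test misses 58–73%. The abstract counts 486 cases, but section III counts 486 filters. If patients contribute several filters each, there are fewer patients and the miss rates rise.

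**3. What an interval shows.** The approximate 95% half-width for a pairwise risk difference is 1.96√[(p₁(1−p₁) + p₂(1−p₂))/162]. For bleeding this is 1.96√[(0.09 + 0.0475)/162] = 5.7 points, against a gap of 5. The others are thrombotic 4.0 (gap 3), infection 7.2 (gap 5) and cardiovascular 5.2 (gap 4). An observed difference equal to the gap would therefore have an interval that includes zero in every case.

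Example: bleeding in 17/162 (10.5%) v 8/162 (4.9%) meets the item 1 bleeding criterion. Fisher P = 0.094 and pairwise chi-square P = 0.061. The difference is 5.6 points, Newcombe 95% CI −0.4 to +11.7 (the simpler Wald interval is −0.2 to +11.3). The interval shows what the P-value hides: the data are compatible with almost no excess and with one more than twice the 5-point gap.

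**4. Item 6 against item 1.** Take interim bleeding of 9/81 v 4/81 v 4/81, that is 11.1% v 4.9% v 4.9%.

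- Item 1: 11.1% exceeds 10%, and the gap of 6.2 points exceeds 5, so terminating that group is to be considered.
- Item 6: p̄ = 17/243 = 0.0700, and X² = 81 × [0.0412² + 2 × 0.0206²] / (0.0700 × 0.9300) = 3.16. On 2 df, P = exp(−3.16/2) = 0.21. If lifespan and the other adverse-event comparisons are also non-significant, the study continues.

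The same data give two directions.

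**The case against.** A reader might infer that the protocol will declare a flow rate safe whenever P > 0.05. The text does not support that reading: item 4 says that incidences are compared in order to assess safety, and the closing line defines significance. Neither says what a non-significant result means.

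A reader might also infer that the significance test is the only safety tool. It is not. Item 1 has a threshold limb that works without a P-value, item 7 of section IV.3 gives the DSMB room to recommend continuing, modifying or stopping, and section X requires periodic cumulative review of adverse events. These are monitoring provisions, though, and the item 1 differences are not carried into the final analysis.

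Nor are the item 1 figures non-inferiority margins. They are introduced as examples, and each combines an absolute rate with a gap. A rule that required the upper confidence limit to lie below the gap, and called everything else inconclusive, would go beyond the document and work badly. Bleeding of 24/162 v 8/162 (Fisher P = 0.005; Newcombe CI +3.4 to +16.6 points) would be labelled inconclusive despite clear harm.

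Low power for secondary safety outcomes is common, chi-square and Fisher tests are conventional, and confidence intervals may be specified in an SAP that is not shown. All of this stands, and it is no reason to enlarge the trial: 80% power for one pairwise comparison would need 435 (bleeding) to 686 (infection) per group. But the protocol itself fixes the test, its purpose and its criterion, and builds non-significance into item 6. Those parts can be criticised as written.

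Finally, continuing is the default course of a trial, so item 6 is not a safety conclusion. That is fair, but it does not remove the clash with item 1.

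**Conclusion.** The point holds in a limited form. The final analysis named in section XI item 4 assesses safety by tests that would miss differences at the item 1 example thresholds 57–72% of the time at 162 per arm, and 77–85% at 81 per arm. A non-significant result cannot carry a safety conclusion by itself.

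The figures rest on independent patients, full arms, and comparator rates obtained by subtracting the stated gap. Fisher's test, 153 per arm or fewer patients than filters would make them worse. Comparing one arm with the other two pooled, which is not planned, would improve the miss rate only to 46–63%.

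Separately, items 1 and 6 can give conflicting directions on the same interim data whenever a threshold is exceeded while lifespan and adverse events are both non-significant. The documents do not support the stronger claim that the protocol equates non-significance with safety.

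**What to change.** **Section XI item 4.** For each event type, make the pairwise risk differences (250 v 200, 150 v 200, 250 v 150 mL/min) with 95% confidence intervals, for example Newcombe, the main safety result. Keep the chi-square or Fisher P-value as supportive. State that P > 0.05 is not evidence of no excess risk, and that an interval wholly above zero is reported as evidence of excess harm. Show the item 1 differences (5, 3, 5 and 4 points) only as a reference for reading the intervals, not as formal margins.

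**Section IV.3.** Give the DSMB the same intervals at the interim. Reconcile item 6 with item 1 so that one set of data cannot call both for continuing and for considering termination of a group. How they are reconciled is for the investigators and the DSMB to decide.

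**Cost.** Some wording and a little more analysis, with no extra patients or data. The intervals will be wide and often inconclusive, which is what a trial of this size can honestly say about these events.
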